### **9.6.5. QuinteT evaluation and optimisation of the recruitment process**

#### *QuinteT Step 1: Understand recruitment as it happens*

**Design and aim:** Qualitative analysis to understand recruitment challenges (e.g., how to present the trial and address patient concerns) to inform how to optimise recruitment processes.

- a. Semi-structured telephone interviews with patients (~20min, optional) and local study staff (~45min).

Participants: Participants who consent to the trial will be offered the optional QuinteT interview as per 9.6.4.

Study staff: Local study staff [CRC surgeons (n~6), cancer nurse specialists (n~6), research nurses (n~8)] will also be provided with interview-specific participant information sheets by the central study team. Informed consent will be in line with section 9.2. The objectives will be in line with 9.6.4.

- b. Audio-recording of recruitment interactions about the trial (as per 9.1) between patients and local study staff (n~20).

The aim of analysing these data is to enrich the interview data above and reduce potential social desirability and recall bias. They will be used to explore study information provision, recruitment techniques, patient concerns, and randomisation decisions to identify recruitment difficulties and improve information provision.

As per 9.1, patients will be referred to a member of the clinical or research team (e.g., research nurse) to discuss the trial. These interactions may take place face to face or over the phone. Any such interaction in which the trial is discussed with potential participants up until their study participation decision (this includes the screening (first study) visit and interactions prior to this) will, with verbal permission, be audio-recorded.

At the completion of the interaction, the patient will be booked in for a screening visit or may decline to take part. Those coming for a screening visit will be asked to provide informed consent for the analysis and storage of the audio-recording of their face-to-face screening visit. If they decline to take part in the trial, the patient will be asked whether they are happy for the audio-recorded interaction to be kept and analysed or whether they prefer that it gets deleted. If they decide that they don't want the audio-recording kept, this will be deleted. If they are happy for the audio-recording to be kept and analysed, participants will need to provide informed consent only for this aspect of the study using the "Consent form only for audio-recording conversations about the CARE study."

- If the interaction occurs over the phone, the member of the research team (e.g., research nurse) will read through the consent form statements to the participant and complete an electronic form on behalf of the participant. The researcher will then electronically sign the form and send it to the participant (via email or by post), so that the participant can keep it for their records.
- If the interaction occurs face to face, the participant will sign the consent as per 9.2.

Audio-recordings will only be transferred to the central study team after informed consent has been obtained.

**c. Assessment of screening logs**

The local study teams will provide fully anonymised screening logs to the central study team. These logs will be assessed using the SEAR (screening, eligibility, approach, and randomisation) framework for identification of screen failures and dropouts.[69]

**Script development:** The analysis of the above will culminate in developing a “script”, aiming to change problematic terms, so that equipoise communication is improved and common concerns are addressed.

***QuinteT Step 2: Feedback and script piloting***

**Design and aim:** Interviews and audio-recordings of the recruitment interactions to determine how the trial is communicated when the script is used and identify necessary iterations.

**Process:** Recruiters (research nurse or member of the clinical/research team) will receive the script and feedback. The recruiter will audio-record the recruitment interaction with the patients while explaining the trial using the script. As per Step 1, patients and local study staff will also be invited for an interview.

**Sampling, recruitment, and consent:** Interviews with a convenience sample of patients ( $n \approx 10$ ) and local study staff ( $n \approx 6$ ) at 3 sites (but purposively selecting sites with lower initial recruitment rates) to allow for rapid improvements. Recruitment and consent will be in line with Step 1.

**Objectives and analysis of interviews:** As per step 1. For staff, interviews will also explore how comfortable they feel using the script.

**Objectives and analysis of audio-recordings of the recruitment interactions ( $n \approx 10$ ):** Following the above methods, this analysis will explore how well recruiters follow the script, communication challenges, and clear words and phrases to explain equipoise without inadvertently showing preferences. Overall, together with examination of screening logs, this will aim to identify whether the script improves recruitment rates in a pre-post analysis.

**Script iteration:** Based on the above findings, the script will be revised and recirculated with feedback.

***QuinteT Step 3: Optimising recruitment***

**Design and aim:** Analysis of audio-recordings of the recruitment interactions in all sites during months 9-16 to fully optimise recruitment and develop a recruitment strategy for the main RCT.

**Sampling, recruitment, consent, and analysis:** As per steps 1-2 with a convenience sample of  $n \approx 6$  audio-recorded recruitment interactions from each site (to explore differences by site) aiming for analysing  $n \approx 35$  interactions.

***QuinteT Step 4: Facilitating enrolment***

**Design and aim:** Semi-structured qualitative interviews (~20min) to identify challenges in starting the intervention in time together with inspection of logs recording time period between randomisation and intervention commencement.

**Interviewees:** Research nurses at each site (n=6) and the dietitians (n=2) delivering the intervention.

**Objectives:** To explore individual and structural factors influencing rapid implementation of the baseline visit, randomisation, and intervention commencement.

**Sampling, recruitment, consent, and analysis:** As per step 1.

### 9.7. Baseline Assessments

The baseline face-to-face assessment will be conducted during the screening visit at each site. It will last approximately 1.5 hours and it will include:

- Demographic questionnaire
- Concomitant medication
- EQ-5D-5L questionnaire
- HADS questionnaire
- Resource use questionnaire
- Height
- Weight and fat-free mass
- 5 times sit to stand test

### 9.8. Subsequent Assessments

The study schedule is available in Appendix B. The window periods will be:

- 5 days for the optional pre-operative follow-up assessment 1 (0 to 4 days post-randomisation)
- 7 days for the pre-operative follow-up assessment 2 (3 days before the time the interview is expected to occur to 3 days after that)
- 4 days for the pre-operative follow-up assessment 3 (From the day of the assessment is expected to occur (4 days pre-operatively) to the day of surgery)
- Between admission and surgery for the pre-operative follow-up assessment 4
- 27-37 days post-operative for the post-operative follow-up assessment scheduled 30 days post-operative
- 3-year follow-up from medical records: 3 years  $\pm$  9 months post-operatively

#### Pre-operative follow -up assessment 1 – all participants (optional)

Optional QuinteT qualitative interview with all patients who consent to the main trial.

#### Pre-operative follow-up assessment 2 – only for participants in the intervention group

Qualitative interviews with intervention participants. Interviews will occur approximately halfway through the programme, so that participants are well into the intervention but not too close to surgery to better capture the whole pre-operative experience.

### Pre-operative follow-up assessment 3 – all participants

This will include the EQ-5D-5L and HADS questionnaires for all participants. In addition, it will include the feedback pre-surgery questionnaire for intervention participants only. Participants will choose to receive either a link to fill in the questionnaires electronically or a paper questionnaire that they can post or bring in clinic on the day of surgery. Participants will receive email and/or phone reminders to facilitate questionnaire completion

### Pre-operative follow-up assessment 4 – all participants

This will include weight and fat-free mass.

### Post-operative follow-up assessment – all participants

Where possible, this face-to-face assessment will occur jointly with the standard clinical follow-up appointment to minimise travel. It will include:

- Post-operative complications reporting
- EQ-5D-5L questionnaire
- EORTC-QLQ-C29 questionnaire (only completed post-operatively as many questions are not relevant pre-operatively)
- HADS questionnaire
- Resource use questionnaire
- Weight and fat-free mass
- 5 times sit to stand test
- Adverse events
- Post-surgery feedback questionnaire

### Staff assessment

A purposive subsample of research and clinical staff will be invited for a 20-minute qualitative interview. Staff will be given an information sheet and provide informed consent prior to interview.

### Long-term follow-up through the hospital medical records

We will extract relevant data collected as part of routine care at each study site for up to 3 years after each participant completes the study. The type and timing of relevant data collected will depend on data availability based on each participant's routine clinical care. This is likely to include weight, morbidity, mortality, disease progression, new diagnoses, medication, re-admission, re-operation, and healthcare resource use.

## **9.9. Sample Handling**

No samples will be taken.

## **9.10. Early Discontinuation/Withdrawal of Participants**

During the course of the study a participant may choose to withdraw early from the intervention at any time. This may happen for several reasons, including but not limited to:

- The occurrence of what the participant perceives as an intolerable AE.
- Inability to comply with study procedures
- Participant decision

Participants in the care as usual group: They may opt out of study assessments but may remain on study follow-up.

Participants in the intervention group: They may stop the intervention and/or study assessments but may remain on study follow-up and will be encouraged to do so.

All participants may also withdraw their consent, meaning that they wish to withdraw from the study completely. In the case of withdrawal from both treatment (i.e., intervention) and active follow up, the following options for a tiered withdrawal from the study will be given to participants and explained in the participant information sheet.

According to the design of the study, option 1 below will be the default. Alternatively, participants can explicitly opt for option 2.

- 1) Participants may withdraw from active follow-up and further communication but allow the study team to continue to access their medical records and any relevant hospital data that is recorded as part of routine standard of care; i.e., CT-Scans, blood results and disease progression data etc.
- 2) Participants can withdraw from the study but permit data obtained up until the point of withdrawal to be retained for use in the study analysis. No further data would be collected after withdrawal.

In addition, the Investigator may discontinue a participant from the intervention at any time if the Investigator considers it necessary for any reason including, but not limited to:

- Participant declining surgery
- Pregnancy
- Ineligibility (either arising during the study or retrospectively having been overlooked at screening)
- Significant protocol deviation
- Significant non-adherence with the intervention or trial requirements
- Clinical decision

The follow-up of participants that have withdrawn from the intervention but not from active follow-up will continue with the standard follow-up assessments of the study.

Data from randomised participants who undergo curative surgery for colorectal cancer will be analysed. Post-randomisation withdrawal from the study will not result in exclusion of the data for that participant from the analysis. However, participants will be replaced as per section 9.3 if

- they have been randomised but have not undergone curative surgery for colorectal cancer
- they have been randomised but deemed ineligible during the study or retrospectively  
or
- they have withdrawn before randomisation.

The type of withdrawal and reason for withdrawal will be recorded in the eCRF.

If the participant is withdrawn due to an AE, the investigator will arrange for frequent telephone calls as agreed with the participant until the AE has resolved or stabilised (also see sections 9.7, 10, and 13.3.2) and up to the point the participant completes the study. If a participant is withdrawn from treatment due to pregnancy the pregnancy will be followed-up to outcome. See the Safety Reporting section below.

The type of withdrawal and reason for withdrawal will be recorded in the eCRF.

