In the CRC setting, weight loss needs to be achieved within the typical 4-week window between decision to treat and surgery. The most reliable and scalable way to achieve this is through a nutritionally-replete, high-protein, low-energy total diet replacement programme with behavioural support (TDR). TDR reliably leads to a mean 7% (SD: 1.8kg) weight loss within 4 weeks in diverse populations with obesity-related diseases, including in older adults with moderate frailty and with atrial fibrillation, and implemented in pragmatic settings.[21-30] A longer version of the programme is currently being tested nationally in the NHS with the aim of remission of type 2 diabetes.[31]

Intentional weight loss is strongly linked with intervention adherence.[32] However, the period around cancer diagnosis is associated with feelings of uncertainty and anxiety.[33, 34] In this context, it is unclear if people with cancer will enrol and adhere to this intensive intervention to the same extent as in less uncertain chronic disease settings. On the other hand, the structured nature of a nutritionally replete dietary intervention may give people a sense of control and empowerment.[35, 36] Patients report their cancer diagnosis being a stimulus for healthier dietary change,[37, 38] but also report making only marginal changes on their own.[39] This highlights the need for support. Small single-arm and randomised trials have shown high feasibility of recruitment (~50%), engagement (~90%), and retention (~85%) to less intensive pre-operative dietary weight loss interventions in breast, prostate, and gastric cancers. These programmes advised an energy-restricted healthy diet or provided partial meal

replacements.[40-43] Whilst these approaches support the feasibility of intervening in the pre-operative cancer setting, they achieved only small weight loss (average: 3kg) with high variability (SD: 4-5kg) that may be insufficient to improve surgical outcomes.

Contrary to this evidence of intentional weight loss in structured programmes, evidence from cohorts suggests that pre-operative weight loss is associated with worse post-operative and long-term outcomes. However, this is most likely to be unintentional weight loss and explained by selection bias due to advanced stage disease.[44]

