### 11.3. Sample Size Determination

With 72 patients (n=36 per arm), the trial will be 90% powered at one-sided 5% level based on the normal approximation approach to detect whether the proportions for the engagement, adherence, and retention criteria in Table 2 are truly above the upper limit of the red zone (>50% engagement, >35% adherence, >65% follow-up) based on an alternative being in the green zone.[70] The collective power for all three criteria is 85% at 5% level, without multiple testing adjustment. Recalculating the sample size on a binomial approach (sensitivity analysis) provided almost identical estimates.[70]

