### 3.3 Sample Size, hypothesis testing, and progression decision

*See also the protocol section "Sample Size Determination"*

With 72 patients (n=36 per arm), the trial will be 90% powered at one-sided 5% level based on the normal approximation approach to detect whether the proportions for the engagement, adherence, and retention criteria in the table 1 are truly above the upper limit of the red zone (>50% engagement, >35% adherence, >65% follow-up) based on an alternative being in the green zone. The collective power for the three criteria of engagement, adherence, and retention is 85% ( $93\% \times 92\% \times 99\%$ ) at 5% level to detect "GO" signals, without multiple testing adjustment. Recalculating the sample size on a binomial approach (sensitivity analysis) provided almost identical estimates.

We are testing against the upper limit of the red zone when the lower limit of the green zone is hypothesised to be true, therefore:

- Null hypothesis: True feasibility outcome is not greater than the upper limit of the red zone.
- Alternative hypothesis: True feasibility outcome is greater than the upper limit of the red zone.

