### 4.2 Definition of Analysis Populations

*See also the protocol section “Analysis populations”*

All randomised and eligible participants that underwent surgery will be included in the main analysis on an intention-to-treat principle regardless of withdrawal or non-adherence. A per protocol analysis will include the subsample of intervention participants who achieved  $\geq 5\%$  weight loss from baseline to the day of surgery. The adverse event analysis will include the participants in the control group and the participants commencing the intervention in the intervention group. Participants who had their surgery less than 20 days since randomisation will be included in this analysis.

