## 3. DEFINITION OF POPULATION FOR ANALYSIS

Main analysis: All randomised participants that underwent surgery will be included in the main analysis on an intention-to-treat basis (ITT) regardless of withdrawal or non-adherence. An intention-to-treat basis assigns all randomised participants to their originally allocated group, whether they received their allocated randomised treatment arm approach or not, or dropped out or not. Participants who had their surgery less than 20 days since randomisation will be included in this analysis.

Per-protocol analysis: We will also conduct an analysis on a per-protocol basis. A per-protocol basis includes only those randomised participants who met all eligibility criteria, had no major deviations from the study procedures, and adhered to their assigned interventions. For the intervention group, this includes the participants who achieved  $\geq 5\%$  weight loss from baseline to the day of surgery. For participants in the usual care group, this excludes those who lost  $\geq 5\%$  weight loss from baseline to the day of surgery. Participants who had their surgery less than 20 days since randomisation will not be included in this analysis.

Adverse events: The adverse event analysis will include the participants in the control group and the participants commencing the intervention in the intervention group.

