## 15.4 Sensitivity Analyses

Sensitivity analyses will be done on at least the following:

- **Per-protocol analysis.** The per-protocol analysis will repeat the above models using the per protocol population as defined in section 3.
- **Stratification factors.** The two stratification factors are performance status (“0” vs “1-2”) and age at diagnosis (“< 70 years” and “ $\geq$ 70 years”). For sensitivity analysis we will do the following:
  - Repeat the models with an interaction term between age at diagnosis (“< 70 years” and “ $\geq$ 70 years”) and treatment. This will be expanded to “...and treatment and time” if time is an input variable, see below.
  - Repeat the models with an interaction term between performance status (“0” vs “1-2”) and treatment. This will be expanded to “...and treatment and time” if time is an input variable, see below.
  - Models measuring the state at one timepoint (eg discharge) or the state change between two timepoints will not need a time variable. Models measuring the state at two or more timepoints (eg baseline vs admission vs 30-days post-op) will need a time variable. In such cases, the interaction above will include the time variable. The paper at [7] is an example of this.
- **Other.** Other sensitivity analyses may be conducted if deemed necessary by the Trial Statistician.

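### The set called intention-to-treat is conditional on surgery, with replacement, so progression criteria 2 to 4 can be inflated; the supplement's per-protocol set makes its weight comparison circular

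*Combined protocol and SAP*

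**What the plan says.** **Main set.** Protocol 9.10 (Early Discontinuation/Withdrawal) restricts analysis to randomised participants who have curative surgery. It replaces a participant if "they have been randomised but have not undergone curative surgery for colorectal cancer", and also one found ineligible during the study or retrospectively. It refers to section 9.3 for replacement, but 9.3 contains no such procedure. Protocol 11.4 and SAP 4.2 use the same label: "All randomised and eligible participants that underwent surgery will be included in the main analysis on an intention-to-treat principle". Section 3 of the SAP supplement on secondary outcomes omits the eligibility condition and keeps the surgery condition. It then explains intention-to-treat as covering every randomised participant, dropouts included.

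**Progression criteria.** Protocol 11.2 and SAP 3.7.1 summarise the criteria over all participants. Neither they nor SAP Table 3 says whether that means randomised or operated. SAP 3.7.1 also says that uncertainty plays no part in the decision, and the worst of criteria 2 to 4 sets the overall signal.

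**Per-protocol set.** Protocol 11.4 and SAP 4.2 name intervention participants with at least 5% loss and give no rule for controls. Supplement section 3 adds one: "For participants in the usual care group, this excludes those who lost" at least 5%. Supplement 15.4 gives the use: "The per-protocol analysis will repeat the above models using the per protocol population as defined in section 3". Those models include weight and fat-free mass.

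**The concern.** Having surgery is a post-randomisation event, and Protocol 9.10 itself anticipates participants who decline it. A definitive trial would randomise patients before anyone knows who will be operated on. A patient lost between randomisation and surgery is therefore a feasibility failure of the kind this trial exists to count. If such patients leave the denominator and are replaced, adherence and retention describe those who completed the pathway, and a signal could read green when the rate among all randomised is amber.

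The per-protocol problem is of another kind. Membership is decided by weight loss, and weight is then compared between the selected groups. A difference follows from the selection rule whether or not the programme works.

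**Working it through.** **1. The plan's own figure.** Inputs: "With 72 patients (n=36 per arm), the trial will be 90% powered at one-sided 5% level" (Protocol 11.3); null values ">50% engagement, >35% adherence, >65% follow-up"; green thresholds of 75%, 60% and 85% (Protocol Table 2). One-sample normal approximation:

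power = Φ{[(p1 − p0)√n − 1.645√(p0(1 − p0))] / √(p1(1 − p1))}

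- Engagement, n = 36, 0.50 against 0.75: 94.1% (SAP 3.3 states 93%).
- Adherence, n = 36, 0.35 against 0.60: 92.8% (92%).
- Retention, n = 72, 0.65 against 0.85: 99.5% (99%).
- Product: 86.9% (the stated 93% × 92% × 99% gives 84.7%, reported as 85%).

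The sample size reproduces to within 2 points. With n = 36 the retention power is 87.8%, so the stated 99% needs all 72 participants.

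**2. Effect of the denominator.** Let d be the share of randomised participants without surgery, and p_op and p_non the success rates with and without surgery. Then

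rate over all randomised = p_op − d(p_op − p_non).

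If p_non = p_op there is no inflation. The worst case is p_non = 0. The documents give no value for d, so a range is assumed:

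| d | Adherence, 60% if operated | Retention, 85% if operated |
|---|---|---|
| 5% | 57% | 80.75% |
| 10% | 54% | 76.5% |
| 15% | 51% | 72.25% |
| 20% | 48% | 68% |

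**3. Whole patients, worst case.** The smallest green counts are 62/72 for retention (61/72 = 84.7%) and 22/36 for adherence (21/36 = 58.3%).

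- Retention: 62/72 = 86.1%. One non-operated patient gives 62/73 = 84.9%, below 85% as written although it rounds to 85%; the plan has no rounding rule. Two give 62/74 = 83.8%, amber either way.
- Adherence: 22/36 = 61.1%. Two non-operated patients give 22/38 = 57.9%, amber.
- At the lower cutoff: 13/36 = 36.1% (amber). Two give 13/38 = 34.2% (red).

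Higher counts survive. With 72 operated participants, d = 5% means about 76 randomised (38 per arm) and d = 10% means 80 (40 per arm). Adherence stays green from 23/38 = 60.5% or 24/40 = 60.0%, and retention from 65/76 = 85.5% or 68/80 = 85.0%.

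**4. Chance of a green adherence signal when the true rate over all randomised is 55%.** Exact binomial, all non-operated patients failing. The operated-only rule needs at least 22 of 36, with success rate 0.55/(1 − d). The all-randomised rule needs at least 60% of n = 38, 40 or 43.

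| d | Operated only | All randomised |
|---|---|---|
| 5% | 42% | 30% |
| 10% | 57% | 32% |
| 15% | 74% | 29% |

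**5. Per-protocol weight comparison.** For percentage loss L ~ N(m, s²) and a = (5 − m)/s:

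E[L | L ≥ 5] = m + s·φ(a)/(1 − Φ(a)); E[L | L < 5] = m − s·φ(a)/Φ(a).

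- No true effect; assumed mean 1%, SD 3% in both arms. a = 1.333, φ = 0.1640, upper tail = 0.0912. Intervention: 1 + 3 × 0.1640/0.0912 = 6.39. Controls: 1 − 3 × 0.1640/0.9088 = 0.46. Difference 5.9 points.
- True effect 5.5 points; assumed 6% (SD 2.5) against 0.5% (SD 2). Intervention: 6 + 2.5 × 0.3683/0.6554 = 7.40. Controls: 0.5 − 2 × 0.0317/0.9878 = 0.44. Difference 7.0 points.

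**6. Other outcomes.** A simulation assumed no effect on complications, a complication rate of about 43%, 60% of intervention patients and 3% of controls at or above 5% loss, and a correlation of 0.5 between weight loss and latent fitness. Selection alone gave differences of 0, −2.6, −4.2 and −6.3 percentage points as the log-odds effect of fitness rose through 0, 0.3, 0.5 and 0.8.

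**The case against.** The strongest reply is that the documents do not establish inflation. The criteria are to be summarised over all participants, and no passage ties criteria 2 to 4 to the operated set. Operated participants who withdraw or do not adhere stay in, missed calls count as non-engagement (SAP 6.3), and the likely baseline carry-forward scores a missing weight as below 5%. All this stands, and it is why the rates *can be* inflated rather than *are*. Protocol 9.10 still points to the operated set, so the ambiguity needs settling.

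Adherence is defined to the day of surgery and retention at 30 days afterwards, so neither has an obvious value without surgery. A patient who lost 5% before a cancelled operation would be scored as non-adherent. Counting non-surgery as failure is one defensible estimand and not the only one; showing both figures answers this.

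Some stronger readings are tempting but unsupported:

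- *A diet-related failure to reach surgery disappears from the primary criteria.* Safety is a primary criterion and must be at least amber before criteria 2 to 4 are read. Its analysis set is all controls plus everyone who starts the intervention, with no surgery condition. Participant flow and withdrawals with reasons are also reported (SAP 5.1, 5.2).
- *The diet could influence every exclusion for ineligibility.* Protocol 9.10 includes ineligibility overlooked at screening, which is a baseline fact.
- *The control exclusion removes patients with advanced disease.* The background does say of pre-operative weight loss: "However, this is most likely to be unintentional weight loss and explained by selection bias due to advanced stage disease". That concerns external cohorts. This trial requires listing for curative resection and excludes self-reported prior loss of 10% or more.

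An operated-only set is also reasonable for operative and complication outcomes.

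**Conclusion.** The point holds in a limited form. The set called intention-to-treat is conditional on surgery, and in the protocol and SAP on eligibility, with replacement. That much is in the text and should be relabelled.

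Inflation of criteria 2 to 4 rests on two conditions: that the operated set is the denominator, and that non-operated patients do worse. The second is plausible for retention and day-of-surgery weight loss, which are both timed from surgery. The changes of signal shown are worst cases near a cutoff under an assumed non-surgery rate; they do not forecast the result.

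The per-protocol comparison is circular for weight. Fat-free mass is derived from weight and body-fat data, so it is closely tied to the same selection. A reader might infer that all per-protocol effects are circular. For complications, stay, quality of life and fitness the problem is selection bias, whose size depends on unknown associations. In the no-effect example only about 9% of the intervention arm (roughly 3 of 36) would qualify, so the 5.9 points show the mechanism and not a likely estimate. The per-protocol set does not enter the progression rule, no p-values are planned, and the protocol and SAP leave its control group undefined.

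**What to change.** - **Criteria 2 to 4.** Compute them over all randomised participants as allocated, using the intervention arm only for engagement and adherence. Count those without surgery as not retained and as not reaching 5% loss. State which calls are due when surgery is cancelled. Report non-surgery counts and reasons by arm, and show the operated-only figures alongside.
- **Main set.** Call the operated set modified intention-to-treat and keep it for operative and complication outcomes. Say whether replaced participants count towards the 72 in criterion 1c, and correct the cross-reference to section 9.3.
- **Per-protocol set.** Do not refit weight or fat-free mass. Do not exclude controls on weight loss. Define intervention adherence by exposure already collected (calls answered, weekly 0 to 100 rating). This still selects on behaviour after randomisation in one arm, so label the result as open to selection bias.
- **Consistency.** Use one definition of each set in the protocol, SAP and supplement, including the eligibility condition.

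The cost is wording in three documents and some extra table rows, with no new data collection. Retention and adherence may look slightly less favourable.
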